|  |  | d. Information system to follow up patients | Pre-existing:   - System for patient register with patient appointment cards | Pre-existing:   - Digital registration - System to trace/follow-up defaulters via mail and telephone (max 3 calls after 1 visit missed) | By SMART2D:   - Manual patient register filled in daily by HCW, with appointment diary, appointment cards and contact information forms - Patient tracking in two steps: 1) by phone to patient   2) via care companion (after each missed visit) |
| **2. Strengthen patient role in self-management** | a. Brief motivational, behavioural coaching for behaviour change | Pre-existing:   - Individual lifestyle counselling by HCW and health education delivered in groups by health promotors   By SMART2D:   - Skill-enhancement / standardization of delivery of motivational, behavioural coaching | Pre-existing:   - Individual lifestyle counselling by HCW   By SMART2D:   - Skill-enhancement / standardization of delivery of motivational, behavioural coaching | By SMART2D:   - Standardized health education and motivational, behavioural coaching in groups by HCW (documented guide provided) |  |
|  | b. Overview of care process and patient role | By SMART2D:   - Patient flowchart - Brief patient info / health education material | By SMART2D:   - Patient flow chart - Patient brochure and care companion role at visit 2 (or enrolment) by smart2d | By SMART2D:   - Brief patient info / health education material at enrolment |  |
|  | c. Access to measuring devices | No self-monitoring devices at facility  By SMART2D:   - Self-monitoring instructions in health education material | By SMART2D:   - Pedometers at visit 2 - Self-monitoring instructions in health education material | No self-monitoring devices at facility  By SMART2D:   - Self-monitoring instructions in health education material |  |

Figure 6: A Flowchart for the SMART2D Facility and Community Intervention as Adapted in South Africa

Figure 7: A Flowchart for the SMART2D Facility and Community Intervention as Adapted in Sweden

Figure 8: A Flowchart for the SMART2D Facility and Community Intervention as Adapted in Uganda

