***Facility baseline evaluations:***

We will conduct baseline facility evaluations that will include:

1. Health facility assessment on the level of staffing with different health care cadres, equipment and supplies, and availability of guidelines relevant for diabetes care
2. A context assessment to assess the opinion and views of facility health care workers regarding facilities in their working environment

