**Recruitment of care companions screening (*to be answered by the patient*)(**[**Knowlton 2003**](#_ENREF_1)**)**

1. Who would you prefer to help you out if you needed help? E.g if you couldn’t take care of yourself, who would you want to stay with?
2. Who do you think will be the most helpful person in your life in dealing with Diabetes/prediabetes?
3. Is there anyone else who would be especially helpful with dealing with diabetes/prediabetes?

**Criteria for selection (*information for clinicians*)(**[**Nachega, Chaisson et al. 2010**](#_ENREF_3)**,** [**Kunutsor, Walley et al. 2011**](#_ENREF_2)**)**

1. Must be living in the patients’ household/neighborhood
2. Aware of patients’ health condition
3. Has accepted patients’ health condition and is a confidant
4. Willing and committed to support patient with care for a long period of time
5. **ROLE OF CARE COMPANIIONS**
6. Remind patients to go for next clinic appointments and peer group sessions.
7. Remind patients to take diabetes medication; observe and record while patient takes at least one dose per day?([Nachega, Chaisson et al. 2010](#_ENREF_3)).
8. Observe and confirm that daily/weekly physical activity goals are met.
9. Ensure a healthy diet for the patient.
10. **TRAINING GUIDELINES**

Patients and their selected care companions will undergo 90 minutes of baseline training on;

1. Diabetes/ prediabetes (causes, diagnosis, signs and symptoms, treatment and control)
2. Diabetes/prediabetes lifestyle (physical activity, diet)
3. Role of care companions

Care companions will receive booster health education every 3 months

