|  | - Make appropriate changes to translated tools. - This is final version to be administered once questions are clarified. |

INSTRUCTIONS to site teams

- This set of data collection tools contains all the generic instruments that should be used during screening/recruitment and baseline.
- All sections are numbered. Kindly do not change the section numbers, question numbers or codes in this version.
- Please provide laminated SHOWCARDS in colour to all data collectors. Instruct data collectors to give the appropriate SHOWCARD for each section to the participant to make it easier for them to respond.
- It is recommended that baseline data collection is staggered over two occasions to decrease participant fatigue and improve the quality of the data collected. Please follow the recommended steps below to divide the baseline data collection in two steps.
  - **During RECRUITMENT visit**

STEP 1 = Section 1 to confirm eligibility 🡺 Sign informed consent 🡺 Section 2 to assign identifiers 🡺 Sections 2-11.2 🡺 Fill in start date for pedometer reading in Section 11.3 🡺 Give instructions on pedometer use + demonstrate use of pedometer + reset and help the participant to wear a masked pedometer 🡺 Confirm instructions and decide on date to collect back the pedometer after 7 days 🡺 If you are unable to collect back the pedometer after 7 days – give specific instructions on what the participant is expected to do 🡺 BREAK off baseline data collection HERE.

- - **During visit to COLLECT PEDOMETER**

STEP 2 = Meet on previously decided date 🡺 Check pedometer and enter reading and end-date in section 11.3 🡺 Complete sections 12-21. END of BASELINE data collection.

About this document

This is a master document containing the complete set of data collection tools that will be administered using a survey methodology. Please note, that evaluations that involve qualitative methodologies are not included here.

The document is divided into four parts:

*Part I: Basic participant data*

*Part II: Intervention process measures (based on Self Determination Theory)*

*Part III: Selected context measures and expenditure*

*Part IV: Process and fidelity checks*

Please note that this document includes tools pertaining to individuals, facilities and local community. It is not meant to be administered together in one visit. Part I includes the set of tools that should be administered together in one baseline/end-line visit.

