**Table 3: Details of tools, sources and data collection points for Part III**

| Questionnaires | Source | BL | M2-11 | EL |
| --- | --- | --- | --- | --- |
| **Out of pocket expenditure: Individual and family questionnaire** | Prepared by [name] | X |  | X |
| **Health facility survey – to be administered to head of health facility*** | Prepared by [name] |  | X |  |
| **EPOCH – to be conducted by researcher and collected one per community*** | Environmental Profile of a Community’s Health (Clara Chow – Population Health Research Institute, Hamilton) |  | X |  |

* Not included in this set of data collection tools

| **SECTION 21: Out of Pocket Expenditure related to type 2 diabetes** | | | |
| --- | --- | --- | --- |
| **SECTION 21A: Out of Pocket Expenditure – Outpatient cost** | | | |
| **S.NO:** | **Questions** | **Response** | **Code** |
| A | Do you usually spend any money on medication and other related costs? | 1 Yes regularly  2 Yes occasionally  0 No  **If NO, SKIP to B** | OOPO_1a |
|  | **In the last month, how much did you spend on the following items in relation to treatment of type 2 diabetes?**  *Please record in respective local currency for each setting: Ug Sh (Uganda)/SAR (South Africa)/SEK (Sweden)* | | |
| B | Medicine:  1. Diabetes medication  2. Other medication | 1. └─┴─┴─┴─┴─┴─┴─┘  2. └─┴─┴─┴─┴─┴─┴─┘ | OOPO_1b1  OOPO_1b2 |
| C | Consultation fees  Not applicable = 888 | └─┴─┴─┴─┴─┴─┴─┘  └──┴──┘ | OOPO_1c |
| D | Laboratory tests  Not applicable = 888 | └─┴─┴─┴─┴─┴─┴─┘  └──┴──┘ | OOPO_1d |
| E | Other supplies  Not applicable = 888 | └─┴─┴─┴─┴─┴─┴─┘  └──┴──┘ | OOPO_1e |
| F | Food while at the health facility  Not applicable = 888 | └─┴─┴─┴─┴─┴─┴─┘  └──┴──┘ | OOPO_1f |
| G | Appreciation of health worker  Not applicable = 888 | └─┴─┴─┴─┴─┴─┴─┘  └──┴──┘ | OOPO_1g |
| H | Transport ( to and from facility)  Not applicable = 888 | └──┴──┘ |  |

O

| **SECTION 21B: Out of Pocket Expenditure – Hospitalisation cost** | | | | | |
| --- | --- | --- | --- | --- | --- |
| I | In the past 12 months, how many times were you hospitalized ? | Number of times └─┴**─┘**  **If 0 SKIP to SECTION 21C** | | | OOPI_1i |
| **For each hospitalization** (max 3 – if more, take last 3) can you answer the following questions | | | | | inst_oopi1 |
|  |  | **1** | **2** | **3** |  |

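### The data collection tools put the facility and community surveys at months 2–11 where the protocol body says baseline, and part of the participant baseline may follow education material given at enrolment

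*Protocol*

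**What the plan says.** **Facility and community surveys.** Section 3.7 announces the facility work as a baseline activity: "We will conduct baseline facility evaluations that will include" an assessment of staffing, equipment, supplies and guidelines, and a context assessment. It also lists the community environment evaluation (EPOC) as part of baseline, and Table 15 marks EPOC at baseline and at no other visit. Table 3 of the data collection tools (Part III) has a row "Health facility survey – to be administered to head of health facility" and a row for EPOCH. Both are marked under M2-11 only, with the baseline and end-line columns blank.

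**Participant baseline.** The instructions to site teams recommend two steps: "It is recommended that baseline data collection is staggered over two occasions to decrease participant fatigue and improve the quality of the data collected". After consent, the recruitment visit covers "Sections 2-11.2" and the masked pedometer is started. The interviewer is then told: "Confirm instructions and decide on date to collect back the pedometer after 7 days". Sections 12–21 are completed at that second contact.

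**Trial material.** Table 5 lists for Uganda "Brief patient info / health education material at enrolment". For Sweden it gives visit 2 or enrolment, and for South Africa it states no time. Appendix 5.2 adds: "Patients and their selected care companions will undergo 90 minutes of baseline training on" diabetes, lifestyle and the companion's role.

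**The concern.** A baseline has to be taken before the thing being evaluated has started to act. Two parts of the plan leave this open.

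The first is at facility level. Secondary objective 2 compares the countries on infrastructure and context at baseline, and section 3.13.2 (item 4) analyses these data as baseline comparisons. The trial itself changes that infrastructure in Uganda. A survey at months 2–11 would credit trial-supplied equipment and guidelines to Uganda's starting position. Outcome j and section 3.13.2 (item 6) also ask for change within contexts, which needs more than one measurement.

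The second is at participant level. Section 3.13.2 (item 6) estimates mean change by arm in perceptions and lifestyle measures. Anything gained between enrolment and a delayed baseline is subtracted from that change. Nothing in the site instructions fixes the order of the education material and the second baseline step.

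**Working it through.** The plan states no figure on this point to reproduce, so the check sets the schedules side by side.

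**1. Facility and community surveys**

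| Instrument | Section 3.7 | Table 15 | Tools Table 3 |
|---|---|---|---|
| Health facility assessment / survey | Baseline | No row | M2-11 only |
| EPOC / EPOCH | Baseline | Baseline only | M2-11 only |

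I take the assessment in section 3.7 and the survey in Table 3 to be the same instrument, as I do EPOC and EPOCH. The names differ slightly and the forms are not reproduced.

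- What the trial changes: section 3.3.2.1 says that missing key elements will be put in place by the trial. For Uganda, Table 5 lists glucometers and strips, an HbA1c analyser, blood pressure machines, scales, guidelines and a patient register as supplied by SMART2D. These are what the facility assessment records.
- Where it bites: Table 5 shows the basic equipment as already present in South Africa and Sweden, so the problem sits in Uganda's intervention facilities. Uganda has nine facilities and three arms. Under equal allocation, which is my assumption, 9 × 2/3 = 6 facilities would be surveyed after being supplied.
- Number of time points for EPOCH: Table 15 gives one and tools Table 3 gives one period. Neither schedules the second measurement that a change requires.

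**2. Participant baseline on the recommended split**

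| Measure | Tools section | Timing |
|---|---|---|
| Diet, self-reported activity, tobacco, alcohol, foot care | 5–9 | Recruitment visit |
| Biochemistry, anthropometry, blood pressure | 10–11.2 | Recruitment visit |
| Masked step count | 11.3 | The 7 days after recruitment |
| Support, self-efficacy, autonomy support, self-regulation, adjustment, satisfaction, quality of life, knowledge | 12–20 | Day 7 or later |

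Uganda's enrolment material therefore comes before Sections 12–20 and before all or most of the pedometer week. The same holds in Sweden wherever the enrolment option is used. The order of the material and the first step within the recruitment visit is not stated. Sections 5–9, however, ask mainly about the preceding week or month.

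**3. Which comparison is exposed**

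The material is a facility strategy, so the facility-only and facility + community arms both receive it and it largely cancels between them. Uganda's current-practice arm does not have the facility package (section 3.2). If the full gain from before exposure to month 12 is G and the part gained before the second step is e, the change score shows G − e and the share lost is e/G. The documents give neither quantity.

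**The case against.** **On the surveys.** The protocol body says baseline, so the tools table may be no more than a slip. Section 3.3.2.1 also has the team review present care before supplying what is missing. This stands as far as it goes: months 2–11 should not be read as the settled schedule. But field teams work from the tools, and nothing names that review as the data source for secondary objective 2. On context change, Table 15 schedules process evaluation at months 3, 6 and 12, and Part III plans narratives of changes over time. Outcome j may therefore have another source, but the plan does not say so.

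**On the participant baseline.** The split is only a recommendation, and sites decide how to administer Parts II and III. Group coaching in Uganda starts at month 3. Section 3.3.3.1 has companions nominated at enrolment, but Table 8 has them identified at month 1 or 3 in Uganda and at visit 2 in Sweden. Section 3.3.3.2 and Table 7 provide no separate companion training, which conflicts with the 90 minutes in Appendix 5.2. Section 3.3.2.3 describes most people in the Uganda study area as illiterate, which limits what a leaflet can do. All of this stands, and it reduces the documented early exposure to the brief material.

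**Stronger readings the documents do not support.**

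- A reader might infer that the behavioural outcomes as a whole have a late baseline. They do not: Sections 5–9 are done at recruitment, and only the step count runs into the following week.
- A reader might infer bias in the facility versus facility + community contrast. The enrolment material is shared by both arms. The companion booklet is tied to a first visit that is not placed before the second baseline step. Section 3.3.3.1 does distribute messages in the community arm at screening events, but these come before every baseline measure alike and do not arise from the split.
- A reader might infer a known loss of effect. Assuming a final gain of 0.5 SD and a first-week gain of 0.1 to 0.3 SD, e/G would be 0.1/0.5 = 20% to 0.3/0.5 = 60%. Neither input has any basis in the documents.

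**Conclusion.** The scheduling contradiction is real and needs no assumption beyond matching the instrument names. If tools Table 3 is followed, secondary objective 2 will not describe baseline for Uganda's intervention facilities. Whichever table is followed, EPOCH alone cannot estimate the change in context named in outcome j.

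The participant part is a risk, not a demonstrated bias. It is confined to the pedometer week and Sections 12–20, at sites that use the split and give material at enrolment. It matters mainly for Uganda's comparison with current practice, and its size is unknown. Secondary and process measures are involved. The HbA1c baseline is taken in the first step and is not affected by the split. The corrections are inexpensive enough to be worth making.

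**What to change.** 1. In Table 3 of the data collection tools, move the health facility survey and EPOCH to baseline, to be completed before trial equipment, guidelines and training are delivered. This aligns the tools with section 3.7 and Table 15 and costs only wording and sequencing.
2. Either repeat EPOCH at end-line, at 9 + 4 + 2 = 15 clusters (section 3.10), or state that outcome j rests on the process evaluation. The repeat is optional extra work; the statement costs nothing.
3. In the instructions to site teams, have Sections 12–20 completed before the education leaflet is handed over, or hand the leaflet over when the pedometer is collected. The first option lengthens the recruitment visit if the leaflet stays there, which works against the reason for the split, and it leaves the pedometer week after the leaflet. The second keeps the split and covers the pedometer week as well, at the cost of the leaflet arriving about a week later. Neither alters clinical care, and coaching and companion support need not be held back.
4. Reconcile the passages on companion timing and training (sections 3.3.3.1 and 3.3.3.2, Tables 7 and 8, Appendix 5.2), so that what participants receive before the second baseline step is clear.

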**Structure of this document**

Each part starts with a table outlining the individual tools included in that section, the sources of the same and the data collection time-points for each. A framework which explains the choice of tools is also included for parts II and III.

**Variable coding strategy and tool formats:** As far as possible, all tools have been converted to a 4-column format – s.no, questions, response and variable code. Variable coding format and characters have been chosen such that they will be accepted in different statistical software packages such as STATA, SPSS, etc. Please ensure that the codes are same for each site – to avoid any problems while merging data. If sites include additional questions to the ones in the generic format, please use different codes to the ones in the generic format.

Each response is coded as a separate variable. All variables (except ID and measurement codes) are coded with the format AAAA_00x.

*For tools that will be administered multiple times (e.g. baseline and end-line):*

- AAAA represents 2-4 alphabets representing the section. E.g. Demographic – DEM;
- 00 represents the month of data collection. E.g. Baseline will be 1, end-line will be 12; and
- x is consecutive alphabets representing question numbers in each section.
- Any sub-questions under each question will be further identified by and underscore + number + alphabet as needed (e.g. _1 or _1a)
- Sometimes additional details are needed and these are added after an underscore.
- E.g. DIET_1a is first question in section on dietary behaviour collected during baseline. When the same variable is collected at end-line, it will be DIET_12a.

*For tools that will be administered only once (e.g. either baseline or end-line):*

- AAAA represents 2-4 alphabets representing the section. E.g. Demographic – DEM;
- 00 represents the question numbers
- x represents any sub-questions under each
- E.g. ELI_2a is first sub-question under question number 2 in the section on eligibility and recruitment check. Sometimes additional details are needed and these are added after an underscore.

PART I: Basic Participant Data

**Table 1: Details of tools, sources and data collection points for Part I**

| Questionnaires | Source | BL | M2-11 | EL |
| --- | --- | --- | --- | --- |
| **Eligibility & Recruitment Check** | - SMART2D | X |  |  |
| **Identification Information** | - SMART2D | X |  |  |
| **Demographic & Socioeconomic Measures** | - WHO STEPs Survey | X |  |  |
| **Medical and Medication History** | - WHO STEPs Survey  - GACD diabetes data dictionary | X |  |  |
| **Behavioural Measures – Diet** | - WHO STEPs Survey  - Summary of Diabetes Self-Care Activities (SDSCA) | X |  | X |
| **Behavioural Measures – Physical Activity** | - Summary of Diabetes Self-Care Activities (SDSCA)  - Single Question Physical Activity Questionnaire (Rose et al) <http://appliedresearch.cancer.gov/paq/q098.html> | X |  | X |
| **Behavioural Measures – Tobacco Use** | - WHO STEPs Survey | X |  | X |
| **Behavioural Measures – Alcohol Consumption** | - WHO STEPs Survey | X |  | X |
| **Other Behavioural Measures – Foot care** | - Summary of Diabetes Self-Care Activities (SDSCA) | X |  | X |
| **Biochemical – FPG^#^** | - WHO STEPs Survey | X | X |  |
| **Biochemical – HbA1c** | - WHO STEPs Survey | X |  | X |
| **Anthropometry and others: Height, weight & Waist circumference** | - WHO STEPs Survey | X |  | X |
| **Anthropometry and others: Blood Pressure** | - WHO STEPs Survey | X |  | X |
| **Anthropometry and others: 7-day pedometer steps** | - SMART2D | X |  | X |
| **Community activities §** | - Kerala Diabetes Prevention Programme |  |  | X |

^#^ FPG measurements will be used for screening in Ug & SA and interim monitoring in Ug

§ Not included in this document – to be finalised before end-line

| **SECTION 1: ELIGIBILITY & RECRUITMENT CHECK**  (Instructions: To be filled in by recruiting personnel before participants sign informed consent) | | | | |
| --- | --- | --- | --- | --- |
| **STEPs** | **Description & questions** | **RESPONSE** | | **CODE** |
|  | REDCAP: Assign the screening ID number | └──┘└──┘└──┘ | | study_id |
| **STEP 1** | **RECRUITMENT algorithm** | **No** | **Yes** |  |
|  | Does the site-specific recruitment algorithm for the screening and diagnostic tests (HbA1c or FPG) for the individual show RECRUIT? | └──┘ | └──┘ | ELI_1 |
|  | "If NO, the subject is NOT ELIGIBLE to be recruited for the trial. Do not continue with recruitment." |  |  | Inst_eli_1 |
| 🡺 If YES, proceed to STEP 2 | | | |  |
| **STEP 2** | **Answer the following ELIGIBILITY questions** | **No** | **Yes** |  |
| a) | Has the individual been a resident in the location of the interview for less than 6 months? | └──┘ | └──┘ | ELI_2a |
| b) | Is the individual less than 30 years, or older than 75 years of age | └──┘ | └──┘ | ELI_2b |
| c) | Has the individual indicated that he/she has plans of migrating out of the study area over the next 12 months? | └──┘ | └──┘ | ELI_2c |
| **For participants with pre-diabetes, SKIP to (e)** | | | | |
| d) | Was the individual diagnosed with diabetes longer than 12 months before being screened for the SMART2D intervention trial?  REDCAP: "FOR INTERVIEWERS: If the participant has pre-diabetes, mark the selection 'Participant has pre-diabetes'" | 0 = No  1 = Yes  2 = Participant has pre-diabetes | | ELI_2d |
| e) | If female, is the individual pregnant?  **If male, SKIP to (f)**  REDCAP: "FOR INTERVIEWERS: If the participant is male, mark the selection Participant is male" | 0 = No  1 = Yes  2 = Participant is male | | ELI_2e |
| f) | Has the individual been diagnosed with heart disease, stroke or peripheral vascular disease/serious mental disorders affecting cognitive functions? | └──┘ | └──┘ | ELI_2f |
| g) | Has any other individual in the same household been enrolled in this study? | └──┘ | └──┘ | ELI_2g |
| h) | Is the individual enrolled in any other study related to diabetes/ self-management | └──┘ | └──┘ | ELI_2h |
| 🡺 If all of the responses in STEP 2 are NO, the subject is ELIGIBLE to be recruited for the trial. If more than one individual in a household is found eligible, apply the KISH methodology (See Appendix 1). | | | | inst_eli_2 |

| **SECTION 2: IDENTIFICATION INFORMATION**  (Instruction: To be included in each set of participant questionnaires) | | | |
| --- | --- | --- | --- |
| **S.NO:** | **Questions** | **Response** | **Code** |
| A | Site Identification Number  UG/SA/SW | └──┘└──┘ | SI_ID |
| B | Cluster/facility Identification number  *Each site to assign numbers to each cluster (SA: 1-2, SW: 1-4, UG: 1-9)* | └──┘ | CL_ID |
| C | Trial arm identification code | 1= Facility only  2 = Facility + community └──┘  3 = No intervention (Uganda only) | TA_ID |
| D | Unique Participant ID number *(Assigned by study team in the field - assign a range of numbers to each cluster)* | └──┘└──┘└──┘ | PA_ID |
| E | To which diagnostic group is the participant recruited? | 1 = Diabetes  2 = Pre-diabetes └──┘ | DX_ID |
| F | Month of visit  0 3 6 9 12 | └─┴─┘ | MTH_ID |

| **SECTION 3: DEMOGRAPHIC & SOCIOECONOMIC MEASURES** | | | |
| --- | --- | --- | --- |
| **S.NO:** | **Questions** | **Response** | **Code** |
| A | What is your year of birth?  Don’t know: 777  Refused to answer: 999  *If participants do not know the year of birth, prompt for nearest estimate* | YYYY └─┴─┴─┴─┘ | DEM_1a |
| B | Sex of participant  Male = 1  Female = 2 | └──┘ | DEM_1b |
| C | What is your highest level of education passed?  1.None  2. School grades <5  3. School grades 5-7  4. School grades 8-10  5. School grades 11-12  6. Vocational training, with school grade > 12 but no university education  7. University-level undergraduate education  7. University-level graduate / post-graduate education  Don’t know 777  Refused to answer 999 | └─┴─┘ | DEM_1c |
| D | What is your current employment?   1. Employed in public sector 2. Employed in private sector 3. Self-employed 4. Daily wage employment 5. Un-employed 6. Retired 7. Petty trader 8. Peasant farmer 9. Other   777. Don’t know  999. Refused to answer | └──┘ | DEM_1d |
|  |  | If 9, specify: _______________ | DEM_1d_other |
| E | In total, how many members reside in your household (share a common kitchen/ share meals/ spend at least/on average 3 nights in a week at your home, including children of whom you have joint custody that live with you full or part time)? | └─┴─┘ | DEM_1e |
|  | "Choose ONE option to report average household income:  "Option 1 - salary per day * number of days of work per month  Option 2 - Salary per month" | 1 = Option 1  2 = Option 2 | inst_dem_1f_opt |
| F | What is the average income of your household?  (Record only ONE option)  *Instruction: Please answer in Ugandan shilling for Uganda, South African Rand in South Africa and Swedish Kroner for Sweden.*  Don’t know code 777  Refused to answer code 999 | OPTION 1:  └─┴─┴─┴─┴─┘/ day * ______no. of days of work per month  OPTION 2:  └─┴─┴─┴─┴─┴─┘/ Month | DEM_1f1  DEM_1f2 |
| G | What is your current marital status?  0 = Never married or cohabited  1 = **Presently** with somebody: Married/cohabiting  2 = **Presently** not with somebody: Separated/Divorced  3 = **Presently** not with somebody: widowed  4=Other | └──┘ | DEM_1g |
|  |  | **If ‘other’, please specify**  **_______________________** | DEM_1g_other |
| H | What is your country of birth?  777 = Don’t know  999 = Refused | **_____________________** | DEM_1h |

| **SECTION 4: MEDICAL AND MEDICATION HISTORY** | | | | |
| --- | --- | --- | --- | --- |
| **S.NO:** | **Questions** | | **Response** | **Code** |
| A | Have you ever been told by a doctor or other health worker that you have raised blood pressure or hypertension?  No = 0  Yes = 1  Don’t know/unsure = 777 | └──┘ | | MED_1a |
| B | Have you ever taken any drugs (medication) for raised blood pressure prescribed by a doctor or other health worker?  No = 0  Yes = 1  Don’t know/unsure = 777  *Ask the participant to only consider drugs for raised blood pressure prescribed by a doctor or other health worker (if possible interviewer to observe medication for confirmation)* | └──┘ | | MED_1b |
| C | Have you ever been told by a doctor or other health worker that you have raised blood sugar or diabetes?  No = 0  Yes = 1  Don’t know/unsure = 777 | └──┘ | | MED_1c |
| D | Have you ever been told by a doctor or other health worker that you have kidney disease?  No = 0  Yes = 1  Don’t know/unsure = 777 | └──┘ | | MED_1d |
| E | Have you developed any foot ulcers in the past year?  No = 0  Yes = 1  Don’t know/unsure = 777 | └──┘ | | MED_1e |
| F | Have you had any loss of vision in the past year?  No = 0  Yes = 1  Don’t know/unsure = 777 | └──┘ | | MED_1f |
| **For participants with pre-diabetes, SKIP to J** | | | | |
| G | Are you currently on any injectable insulin?  No = 0  Yes = 1  Don’t know/unsure = 777  If, NO, skip to I | └──┘ | | MED_1g |
| H | Are you currently on any injectables other than insulin?  No = 0  Yes = 1  Don’t know/unsure = 777 | └──┘ | | MED_1h |
| I | Are you currently on any oral hypoglycemic agents  No = 0  Yes = 1  Don’t know/unsure = 777 | └──┘ | | MED_1i |
| J | Are you currently on any traditional or complementary medicines to treat or prevent diabetes or pre-diabetes?  No = 0  Yes = 1  Don’t know/unsure = 777 | └──┘ | | MED_1j |

| **SECTION 5: BEHAVIOURAL MEASURES – DIET** | | | | | |
| --- | --- | --- | --- | --- | --- |
| The next questions ask about the fruits and vegetables that you usually eat. I have a nutrition card here that shows you some portion sizes of the foods we are talking about. Each picture represents the size of a serving. As you answer these questions please think of a TYPICAL WEEK and a TYPICAL DAY in the LAST MONTH.  *(Use the SHOW CARDS provided - Important for interviewers to show the right card for the right question as indicated: so for whole fruit – show card 1, for cut fruits show card 2, etc. Each show card represents 1 serving of the food indicated.)* | | | | | inst_diet1 |
| **S.NO:** | **Question** | | **Response** | **Code** | |
| A | In a typical week, on how many days do you eat **fruit**?  Don’t know 777 | | Number of days└─┴─┘ *If zero, go to C* | DIET_1a | |
| B | 1. How many servings of **whole fruit** do you eat on a typical day? (SHOWCARD 1)  Don’t know 777  2. How many servings of **cut or small fruit (fresh or frozen)** do you eat on a typical day? (SHOWCARD 2)  Don’t know 777  3. How many servings of **canned fruit** do you eat on a typical day? (SHOWCARD 2)  Don’t know 777  4. How many servings of **dried fruits** do you eat on a typical day? (SHOWCARD 4) | | Number of servings:  1. └─┴─┘.└─┴─┘  2. └─┴─┘.└─┴─┘  3. └─┴─┘.└─┴─┘  4. └─┴─┘.└─┴─┘ | DIET_1b1,2,3,4 | |
| C | In a typical week, on how many days do you eat **vegetables** like tomatoes, carrots, onions, etc. (excluding tubers and high starch vegetables such as cassava, potatoes, matoke, yams, sweet potatoes)?  Don’t know 777 | | Number of days └─┴─┘ *If zero, go to E* | DIET_1c | |
| D | 1. How many servings of **cut vegetables (fresh or frozen)** do you eat on a typical day?  (SHOWCARD 2)  Don’t know 777  2. How many servings of **canned vegetables** do you eat on a typical day? (SHOWCARD 2)  Don’t know 777  3. How many servings of **uncooked leafy vegetables** do you eat on a typical day?  (SHOWCARD 1) | | Number of servings:  1. └─┴─┘.└─┴─┘  2. └─┴─┘.└─┴─┘  3. └─┴─┘.└─┴─┘ | DIET_1d1,2,3 | |
| E | In a typical week, how many days do you eat **tubers and high starch vegetables (**such as cassava, potatoes, matoke/plantain, yams, sweet potatoes)?  Don’t know 777 | | Number of days└─┴─┘ *If zero, go to G* | DIET_1e | |
| F | How many servings of **tubers and high starch vegetables** do you eat on one of those days? (Such as cassava, potatoes, matoke/plantain, yams, sweet potatoes) (SHOWCARD 1)  Don’t know 777 | | Number of servings└─┴─┘.└─┴─┘ | DIET_1f | |
| G | In a typical week, how many days do you eat **refined starch products**, (such as white rice, pasta, white breads, maize meal, cassava flour meal, pap)?  Don’t know 777 | | Number of days└─┴─┘ *If zero, go to K* | DIET_1g | |
| H | 1. "How many servings of bread do you eat on a typical day?" (SHOWCARD 3)  Don’t know 777  2. "How many servings of other refined starch products (such as white rice, pasta, maize meal pap) do you eat on a typical day?” (SHOWCARD 1)  Don’t know 777 | | Number of servings:   1. └─┴─┘.└─┴─┘ 2. └─┴─┘.└─┴─┘ | DIET_1h1,2 | |
| I | In a typical week, how many days do you eat **non-refined starch** (such as brown rice, whole grain pasta, wholegrain cereal, samp or whole meal/whole wheat / brown breads)?  Don’t know 777 | | Number of days└─┴─┘ *If zero, go to M* | DIET_1i | |
| J | 1. "How many servings of non-refined bread do you eat on a typical day?" (SHOWCARD 3)  Don’t know 777  2. "How many servings of other non-refined starch products (such as brown rice, whole grain pasta, wholegrain cereal, samp or whole meal) do you eat on a typical day?" (SHOWCARD 1)  Don’t know 777 | | Number of servings:   1. └─┴─┘.└─┴─┘ 2. └─┴─┘.└─┴─┘ | DIET_1j1,2 | |
| K | In a typical week, how many days do you eat **fish**?  Don’t know 777 | | Number of days└─┴─┘ *If zero, go to O* | DIET_1k | |
| L | How many servings of **fish**, do you eat on one of those days?  (SHOWCARD 3)  Don’t know 777 | | Number of servings└─┴─┘.└─┴─┘ | DIET_1l | |
| The next questions ask about the way you most often prepare different types of food in your household. | | | | | |
| M | Which cooking method do you usually use when preparing chicken?  1 = Grill/Oven/Roast  2 = Fry  3 = Boil  4 = Steam  5 = Other (specify) | | └──┘  If 5, please specify  **_____________________** | DIET_1m  DIET_1m_other | |
| N | Which cooking method do you usually use when preparing other meat?  1 = Grill/Oven/Roast  2 = Fry  3 = Boil  4 = Steam  5 = Other (specify) | | └──┘  If 5, please specify  **___________________** | DIET_1n  DIET_1n_other | |
| O | Which cooking method do you usually use when preparing fish?  1 = Grill/Oven/Roast  2 = Fry  3 = Boil  4 = Steam  5 = Other (specify) | | └──┘  If 5, please specify  **___________________** | DIET_1o  DIET_1o_other | |
| P | Which cooking method do you usually use when preparing vegetables?  1 = Grill/Oven/Roast  2 = Fry  3 = Boil  4 = Steam  5 = Other (specify) | | └──┘  If 5, please specify  **___________________** | DIET_1p  DIET_1p_other | |
| The next questions ask about the oil or fat that is most often used for meal preparation in your household, and about meals that you eat outside a home. | | | **How often** do you use the following **oils and fats** in your household? | inst_diet3 | |
| Q | | Use the scale below:  1 = Daily  2 = 5-6 days per week  3 = 2-4 days per week  4 = 1-2 days per week  5 = 1-3 days per month  6 = Occasionally, usually less than once a month  7 = Never  Don’t know 777 | 1. Vegetable oil └──┘ 2. Lard or suet └──┘ 3. Butter or ghee └──┘ 4. Margarine └──┘ 5. Mixed butter + oil combination └──┘ 6. Other └──┘If Other, specify below   Other, please specify  ____________________________ | DIET_1q_1-6 | |
|  |  |  |  | DIET_1q_other | |
| R | | On average, how often do you eat meals that were **not prepared at a home**? (By meal, we mean breakfast, lunch or dinner)  1 = Daily = 1  2 = 5-6 days per week  3 = 2-4 days per week  4 = 1-2 days per week  5 = 1-3 days per month  6 = Occasionally, usually less than once a month  7 = Never  Don’t know 777 | └──┘ | DIET_1r | |
| S | | In a typical week, on how many days do you drink **sugar-sweetened beverages** (such as sodas, and other non-carbonated commercially prepared fruit drinks)?  Don’t know 777 | Number of days└─┴─┘ *If zero, go to SECTION 6* | DIET_1s | |
| T | | How many servings of **sweetened non-carbonated drinks** (ready to drink diluted cordials and syrups/commercially prepared sweetened fruit drinks) do you drink on a typical day? | | inst_diet2a | |
|  |  | (SHOWCARD 5)  *Enter the number of drinks consumed per category as shown in the show card.*  Don’t know 777 | 1.a Number of Showcard 5.1 drinks consumed: └──┘.└─┴─┘  1.a.total: Amount in mL of Showcard 5.1 drinks consumed: ____”  1.b Number of Showcard 5.2 drinks consumed: └──┘.└─┴─┘  1.b.total: Amount in mL of Showcard 5.2 drinks consumed: ____”  1.c Number of Showcard 5.3 drinks consumed: └──┘.└─┴─┘  1.c.total: Amount in mL of Showcard 5.3 drinks consumed: ____”  1.d Number of Showcard 5.4 drinks consumed: └──┘.└─┴─┘  1.d.total: Amount in mL of Showcard 5.4 drinks consumed: ____”  1.e Number of Showcard 5.5 drinks consumed: └──┘.└─┴─┘  1.e.total: Amount in mL of Showcard 5.5 drinks consumed: ____”  1.f Number of Showcard 5.6 drinks consumed:└──┘.└─┴─┘  1.f.total: Amount in mL of Showcard 5.6 drinks consumed: ____” | DIET_1t1a,1b..2a,  2b,..  diet_1t1a_total, diet_1t1b_total, diet_1t1c_total,…. | |
|  |  | How many servings of **sugar-sweetened fizzy drinks** (sodas) do you drink on a typical day? | | inst_diet2b | |
|  |  | (SHOWCARD 5)  *Enter the number of drinks consumed per category as shown in the show card.*  Don’t know 777 | 2.a Number of Showcard 5.1 drinks consumed: └──┘.└─┴─┘  2.a.total: Amount in mL of Showcard 5.1 drinks consumed: ____”  2.b Number of Showcard 5.2 drinks consumed: └──┘.└─┴─┘  2.b.total: Amount in mL of Showcard 5.2 drinks consumed: ____”  2.c Number of Showcard 5.3 drinks consumed: └──┘.└─┴─┘  2.c.total: Amount in mL of Showcard 5.3 drinks consumed: ____”  2.d Number of Showcard 5.4 drinks consumed: └──┘.└─┴─┘  2.d.total: Amount in mL of Showcard 5.4 drinks consumed: ____”  2.e Number of Showcard 5.5 drinks consumed: └──┘.└─┴─┘  2.e.total: Amount in mL of Showcard 5.5 drinks consumed: ____”  2.f Number of Showcard 5.6 drinks consumed:└──┘.└─┴─┘  2.f.total: Amount in mL of Showcard 5.6 drinks consumed: ____” | DIET_1t2a,2b,2c,  2d,..  diet_1t2a_total, diet_1t2b_total, diet_1t2c_total,…. | |

| **SECTION 6: BEHAVIOURAL MEASURES – PHYSICAL ACTIVITY** | | | |
| --- | --- | --- | --- |
| **S.NO:** | **Question** | **Response** | **Code** |
| Please think about the last ONE MONTH and the last SEVEN DAYS when you answer these questions. | | | |
| A | On how many of the last SEVEN DAYS did you do **vigorous activities** for **at least 15 minutes**, such as cycling uphill or at fast pace; swimming laps; carrying heavy loads; shovelling or digging; jogging; running or a sport?  0 1 2 3 4 5 6 7 | └──┘ | PA_1a |
